### Study population

Overall, a maximum of 53 patients will be included. Of them, a maximum of 24 will be treated in the dose escalation phase and 41 patients in the phase II part of the study.

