**Fig. 1 Fig1:**
[figure not shown]
Accelerated titration design of the phase I part of the trial. Illustration of the accelerated titration design of the phase I part of the trial. Each box outlined in bold represents a cohort containing the indicated number of patients treated at a given dose level. Ixazomib will be administrated orally on days 1, 8, and 15 and carboplatin intravenously on days 1, 8, and 15 of a 4-week cycle. Drug dosages per dose level are given on the left side of the graph. DLT = dose-limiting toxicity; AUC = area under the curve

**Table 1 Tab1:** Drug dosages per dose level

Dose level	Ixazomib orally on days 1, 8, 15 every 4 weeks	Carboplatin i.v. on days 1,8 and 15 every 4 weeks
1	3 mg	AUC 1.5
2	3 mg	AUC 2
3	4 mg	AUC 2
4	4 mg	AUC 2.5

AUC = area under the curve

The maximum-administered dose (MAD) is defined as the dose at which DLT or 3 moderate toxicities occur in at least two of six patients treated at that dose level. The dose-level just below the MAD is considered the maximum-tolerated dose (MTD), providing that DLT or 3 moderate toxicities are observed in fewer than two of six treated patients (or fewer than one third if more than six patients will be treated) at that dose level. Determination of MAD and MTD is based on DLT or 3 moderate toxicities observed during the first treatment cycle.

Beginning with the 2nd cycle an intra-patient dose escalation is allowed. This is separate from the alternate dose escalation design of the phase I part. If the nadir ANC was ≥500/mL, the nadir platelet count ≥50,000/mL, and non-hematologic toxicities were grade ≤ 1 in the previous cycle, the current dose level can be escalated by one dose level by each cycle. After completion of phase I, all patients, that are treated with a dose below the determined MTD, can be dose escalated at the discretion of the investigator [39, 41].

After establishing MTD in phase I, accrual continues in phase II to evaluate the efficacy and safety of the combination therapy. A total of 41 evaluable patients will be included (patients enrolled in the phase I part within the conventional dose escalation phase at the dose level considered as the MTD may be included).

All subjects will continue on study drugs until disease progression, unacceptable toxicity or treatment discontinuation for any other reason, respectively.

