Assuming a 10% drop-out rate, 46 patients have to be enrolled for phase 2. The maximum number of patients through phases I and II combined will be 53.

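### The overall maximum of 53 patients does not reconcile with the plan's own figures of 24 for dose escalation and 41 evaluable / 46 enrolled for phase II

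*Protocol article*

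**What the plan says.** The protocol article gives four head counts.

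- **Overall maximum.** Methods, Study population: "Overall, a maximum of 53 patients will be included". Determination of sample size repeats it: "The maximum number of patients through phases I and II combined will be 53".
- **Components.** Study population adds that "a maximum of 24 will be treated in the dose escalation phase and 41 patients in the phase II part".
- **Phase II, evaluable.** Study design, in the text after Table 1: "A total of 41 evaluable patients will be included".
- **Phase II, enrolled.** Determination of sample size: "Assuming a 10% drop-out rate, 46 patients have to be enrolled for phase 2".

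The phases may share patients, but only some. Study design says that "patients enrolled in the phase I part within the conventional dose escalation phase at the dose level considered as the MTD may be included".

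The rule for the maximum-administered dose (MAD) works on cohorts of six: it is the dose at which "DLT or 3 moderate toxicities occur in at least two of six patients treated at that dose level". The MTD definition that follows also allows for a level with more than six patients, without giving a number.

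The article does not show how 53 was derived, how many patients are assumed to overlap, or what happens if 53 is reached before 41 are evaluable.

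**The concern.** A figure stated as a maximum should hold when each component is at its own stated maximum. Here it holds only with a larger overlap than the article describes. If escalation runs long, two stated figures then conflict: stopping at 53 can leave phase II short of the 41 evaluable patients on which the 12-response rule and its 80% power rest, while completing phase II exceeds the stated maximum. The article does not say which figure prevails.

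**Working it through.** **1. Components that reproduce**

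- Two-stage rule (at least 5 responses in 22, then at least 12 in 41). P(success) = Σ over x = 5 to 22 of Bin(x; 22, p) × P(Y ≥ 12 − x), with Y ~ Bin(19, p). At p = 0.20 this is 0.096 and at p = 0.35 it is 0.804, against the stated α = 0.10 and power 0.80.
- Enrolment: 41 / 0.9 = 45.6, rounded up to 46.
- Dose escalation: 4 levels × 6 patients = 24. The article does not give this derivation; it is the natural reading.

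**2. The combined maximum**

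Total = phase I + phase II − patients counted in both.

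| Overlap | 24 + 41 − overlap | 24 + 46 − overlap |
|---|---|---|
| 0 | 65 | 70 |
| 6 | 59 | 64 |
| 12 | 53 | 58 |
| 17 | 48 | 53 |

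So 53 needs an overlap of 12 with 41, or 17 with 46.

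**3. When the cap binds**

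If every MTD-level patient counts in phase II, total = patients off the MTD level + phase II. Then 53 allows 53 − 41 = 12 patients off the MTD level with 41, and 53 − 46 = 7 with 46. Escalation paths with six per conventional cohort and one per accelerated cohort:

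| Patients at levels 1 / 2 / 3 / 4 | MTD level | Phase I | Off MTD | Total with 41 | Total with 46 | Phase II places under 53 |
|---|---|---|---|---|---|---|
| 1 / 1 / 1 / 6 | 4 | 9 | 3 | 44 | 49 | 50 |
| 1 / 1 / 6 / 6 | 3 | 14 | 8 | 49 | 54 | 45 |
| 1 / 6 / 6 / 6 | 3 | 19 | 13 | 54 | 59 | 40 |
| 6 / 6 / 6 / 6 | 3 | 24 | 18 | 59 | 64 | 35 |

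The first path fits. The second exceeds 53 by one with 46 enrolled; its 45 places give 45 × 0.9 = 40.5 evaluable. The third leaves 40 places even without drop-out.

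**4. Effect on the decision rule if phase II stops early**

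The formula in step 1, with stage 1 unchanged (5 of 22) and final size n:

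| Final n | Responses required | α at 0.20 | Power at 0.35 |
|---|---|---|---|
| 41 | 12 | 0.096 | 0.804 |
| 40 | 12 | 0.083 | 0.779 |
| 35 | 12 | 0.034 | 0.596 |
| 35 | 11 | 0.073 | 0.721 |
| 35 | 10 | 0.138 | 0.819 |

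At n = 35, with this first stage, no cutoff meets both α ≤ 0.10 and power ≥ 0.80.

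**The case against.** **24 and 41 are not meant to be added.** True: the overlap clause must be credited, so 65 against 53 proves nothing by itself.

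**The overlap is not limited to six.** A reader might infer such a limit from 4 × 6 = 24, but the article states neither that product nor a ceiling on the MTD cohort, and it foresees more than six there. Twelve at the MTD level would give 24 + 41 − 12 = 53 exactly. Fig. 1, not available here, may show cohort sizes. This is the best defence, and it rescues 53 with 41 patients. It does not rescue 53 with the 46 that the preceding sentence in Determination of sample size requires: that gives 58, and reaching 53 would put 17 of the 24 escalation patients at one level.

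**41 against 46.** A reader might infer a contradiction. There is none: 41 are evaluable and 46 enrolled. Study population merely leaves out the word evaluable, though it does so beside a head-count maximum.

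**Phase II will be truncated and its power lost.** A reader might infer this too. The article does not say that the cap overrides phase II, and it plans second-stage enrolment up to 41. Any shortfall depends on a long escalation. The futility stop also ends accrual at 22 with probability 0.54 if the true response rate is 20%, and the cap then never binds.

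**The extreme is rare.** The article gives no DLT rates by level. Under three assumed curves (5–20%, 10–35% and 15–40% across levels), simulation put 18 patients off the MTD level in about 0.5%, 2% and 3.5% of trials. Adding full drop-out (about 31 evaluable) and keeping the cutoff at 12 gives power near 0.40, but that stacks three unfavourable conditions. A cutoff of 10 at n = 31 gives power 0.69 with α 0.074.

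**An implied phase I ceiling.** A reader might infer that 53 limits phase I to 53 − 46 + 6 = 13. The text implies no such limit: what matters is the number of patients off the MTD level. The 14-patient path above would already breach it.

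**Conclusion.** The point stands as a failure of stated figures to reconcile. With six MTD-level patients counted twice, the maximum is 59 (41 in phase II) or 64 (46 enrolled); with none, it is 65 or 70. The most generous reading, 12 counted twice, matches 53 only if the drop-out allowance is ignored.

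The consequence is conditional. Short escalations fit under 53. Being one evaluable patient short costs little (power 0.78). The extreme of 35 costs more (0.60, or 0.72 with a cutoff of 11), but is rare under the toxicity curves assumed. These powers assume that the cap is obeyed and that the first-stage rule is unchanged.

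No test or decision rule is wrong, so this is a correction that should be made, not a flaw in the design. The totals of 59 and 64 rest on six patients per level, which is inferred. Because overlap is only permitted ("within the conventional dose escalation phase at the dose level considered as the MTD may be included"), and a patient treated at that level in the accelerated phase is not covered by the clause, it may be smaller than six.

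**What to change.** 1. State the assumed overlap between phases and restate the combined maximum to match it, in both places where 53 appears: for example 64 with 46 enrolled and six overlapping, or 70 if none overlap. If 53 is kept, show the derivation that reconciles it with 24 and 46.
2. In Study population, give phase II as 46 enrolled / 41 evaluable.
3. State that the overall maximum does not truncate phase II below the 41 evaluable patients that the Simon rule needs.

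The cost is a correction of stated figures, by amendment if the full protocol carries the same numbers. The phase II design, its cutoffs and its planned size do not change.

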### Patients

Patients with metastatic histologically confirmed triple-negative adenocarcinoma of the breast will be assessed for eligibility. Detailed inclusion and exclusion criteria are listed in Table 2. Patients with locally advanced disease are eligible provided they cannot be offered a potentially curative loco-regional treatment option. TNBC is defined by the absence of staining for estrogen receptor (IHC < 1%), progesterone receptor (IHC < 1%) and HER2/neu (IHC 1+ or ISH ratio of < 2.0 between HER2 gene copy number and centromere of chromosome 17 or a copy number of 4 or less [42]). A signed informed consent, with the understanding that consent may be withdrawn at any time without prejudice to future medical care, have to be provided prior to any study-specific procedure. All patients must be female and aged 18 or older with a performance status of ECOG 0–2 and a life expectancy of at least 12 weeks. A disease progression with at least one measurable lesion according to RECIST 1.1 criteria must be documented. Patients must be pretreated with at least one prior line of chemotherapy for advanced disease or a progression must have occurred within 12 months of completion of adjuvant chemotherapy. Women of childbearing potential must have a negative pregnancy test at screening and agree to practice 2 effective methods of contraception, at the same time. An adequate left ventricular ejection fraction at baseline, defined as LVEF ≥50% by either echocardiogram or MUGA and adequate hematological, liver and renal function (absolute neutrophil count ≥1.5 × 10^9^/L, hemoglobin ≥8 g/dL, platelets ≥100 × 10^9^/L, albumin ≥2.5 g/dL, serum bilirubin ≤2 mg/dL, aspartate transaminase and alanine transaminase ≤3 x ULN without liver metastases and ≤ 5 x ULN with documented liver metastases, and serum creatinine ≤1.5 mg/dL or calculated creatinine clearance ≥50 ml/min) is required. If present, a peripheral neuropathy must be less or equal to grade 1 or grade 2 without pain.

**Table 2 Tab2:** Detailed Inclusion and Exclusion criteria

Inclusion criteria	Exclusion criteria
Each patient must meet all of the following inclusion criteria to be enrolled in the study: • Metastatic or locally advanced (without curative loco-regional treatment options with curative intention) adenocarcinoma of the breast, histologically confirmed • Triple-negative subtype defined as the absence of staining for estrogen receptor (IHC < 1%), progesterone receptor (IHC < 1%) and HER2/neu (IHC 0–1+, or 2+ if FISH-test is negative, or ISH ratio of < 2.0 between Her2 gene copy number and centromere of chromosome 17 or a copy number of 4 or less) • Signed informed consent prior to any study-specific procedure, with the understanding that consent may be withdrawn at any time without prejudice to future medical care • Female patients, age ≥ 18 years • Women of childbearing potential must have a negative pregnancy test at screening and agree to practice 2 effective methods of contraception, at the same time, from the time of signing the informed consent form through 90 days after the last dose of study drug OR agree to practice true abstinence when this is in line with the preferred and usual lifestyle of the subject (Periodic abstinence [eg, calendar, ovulation, symptothermal, post-ovulation methods] and withdrawal are not acceptable methods of contraception. • At least one prior line of chemotherapy for metastatic or locally advanced disease or disease progression within 12 months of completion of adjuvant chemotherapy • Documented disease progression • At least one measurable lesion according to RECIST 1.1 criteria • Life expectancy of at least 12 weeks • Performance status ECOG 0–2 • Adequate left ventricular ejection fraction at baseline, defined as LVEF ≥50% by either echocardiogram or MUGA • Peripheral neuropathy NCI CTCAE grade ≤ 1 or grade 2 if no pain on clinical examination • Adequate hematological, liver and renal function: Hematologic: ANC (absolute neutrophil count) ≥ 1.5 × 109/L Hemoglobin ≥8 g/dL Platelets ≥100 × 109/L Liver Function: Albumin ≥2.5 g/dL Serum bilirubin ≤2 mg/dL AST and ALT ≤3 x ULN without liver metastases and ≤ 5 x ULN with documented liver metastases Renal Function: Serum creatinin ≤1.5 mg/dL or calculated creatinin clearance ≥50	Patients meeting any of the following exclusion criteria are not to be enrolled in the study. • Pregnant or lactating women • Serious medical or psychiatric disorders that would interfere with the patient’s safety or informed consent • Clinically significant cardiovascular disease, requiring medication during the study and which might interfere with regularity of the study treatment, or not controlled by medication. • Radiation of the target lesion within the last 4 weeks prior to randomization • Prior radiation to ≥30% of bone marrow • Active bacterial, viral or fungal infection • Known HIV infection • Patients with clinically apparent brain metastases or evidence of a spinal cord compression • Major surgery within 14 days before enrollment • Systemic treatment, within 14 days before the first dose of ixazomib, with strong CYP3A inducers (rifampin, rifapentine, rifabutin, carbamazepine, phenytoin, phenobarbital), or use of *Ginkgo biloba* or St. John’s wort. • Participation in other clinical trials, including those with other investigational agents not included in this trial, within 30 days of the start of this trial and throughout the duration of this trial • Patients that have previously been treated with ixazomib, or participated in a study with ixazomib whether treated with ixazomib or not • History of other malignancy; patients who have been disease-free for 5 years or patients with a history of completely resected non-melanoma skin cancer or successfully treated in situ carcinoma are eligible • Prior treatment with a platinum derivative (except in (neo-)adjuvant setting if breast cancer recurrence did not occur within 12 months after (neo-)adjuvant chemotherapy completion) and/or with a proteasome inhibitor • Known hypersensitivity to the study drugs

Patients with at least one of the following conditions or pretreatments are excluded from trial participation: serious medical or psychiatric disorders interfering with patient’s safety or informed consent, lactating patients, radiation of the target lesion within the last 4 weeks before enrollment, prior radiation to ≥30% of bone marrow, active bacterial, viral or fungal infections, known HIV infection, major surgery within 14 days before enrollment, clinically apparent brain metastases or evidence of a spinal cord compression, systemic treatment with strong CYP3A inducers or use of *Ginkgo biloba* or St. John’s wort within 14 days before the first dose of ixazomib, previous treatment with a proteasome inhibitor or with a platinum derivative unless applied in the (neo-)adjuvant setting if breast cancer recurred later than 12 months after (neo-)adjuvant chemotherapy completion, participation in other clinical trials, application of any investigational agents within 30 days of the start and throughout the duration of this trial, history of another malignancy unless disease-free for ≥5 years or with a history of completely resected non-melanoma skin cancer or a successfully treated in situ carcinoma.

### Translational research program

In a translational research project accompanying the MBC-10 clinical study, predictive markers for treatment response to the investigated drug combination of ixazomib plus carboplatin will be evaluated. Further, analyses of resistance mechanisms are planned. Therefore, somatic as well as germline mutations in BRCA1 and BRCA2, BRCA1/2 methylation status, circulating tumor DNA (ctDNA), gene expression profiles and microRNA expressions will be analyzed from tumor tissue and blood samples, respectively. For further analyses, patients´ blood samples (ETDA and serum) will be collected before treatment start, on day 8 of the first four-weekly treatment cycle as well as on day 1 of every subsequent treatment cycle and at the end of study.

### Determination of sample size

In phase I, an accelerated dose-escalation scheme will be used as outlined above. Single patient cohorts will be enrolled until one dose limiting toxicity (DLT) or 3 moderate toxicities are observed until a certain dose level is reached. Toxicities will be classified according to Common Terminology Criteria for Adverse Events (CTCAE) Version 4.03 [43]. At this dose level the cohort is expanded to three patients and dose escalation reverts to a conventional 3 + 3 escalation design. The 3 + 3 design is rule-based with a statistical power of greater than 87% to detect at least one out of three patients with a DLT or 3 moderate toxicities when the probability for a DLT is 50%.

In the phase II study a single-arm two-stage Simon’s design will be used to allow for early termination if unsatisfactory efficacy results are observed. Sample size estimation is based on overall response rate (ORR).

In a large randomized phase III trial carboplatin was compared with docetaxel as first line treatment in patients with triple-negative breast cancer [20]. In the carboplatin group overall response rate as the primary endpoint of this trial was 31.4% (59/188). In our trial, the investigated drug combination will be mainly tested as second or third-line treatment, and response rates are well known to decrease with increasing lines of therapies [44]. Based on these findings, we would expect an ORR of 20 to 25% for a carboplatin monotherapy, and consider a 35–40% response rate a clinically meaningful improvement [45].

In the phase II part of the study a single-arm two-stage Simon’s Design will be used to allow for early termination if unsatisfactory efficacy results are observed. Sample size estimation is based on overall response rate (ORR).

In a two-stage Simon’s design testing a null hypothesis proportion of 0.2 versus an alternative hypothesis proportion of 0.35 in ORR with α = 0.1 and 1-β = 0.80 a total of 41 patients will be required. In the first stage, 22 patients will be accrued and treated. The study will be stopped if there are fewer than five patients with either CR or PR. If there are at least five responses an additional 19 patients will be enrolled and treated until a total of 41 patients. The regimen is concluded to be effective if 12 or more responses out of 41 are observed at the end of the trial.

Assuming a 10% drop-out rate, 46 patients have to be enrolled for phase 2. The maximum number of patients through phases I and II combined will be 53.

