### Efficacy analysis

ORR will be assessed according to RECIST v1.1 [46] and comprise partial response (PR) or better occurring during any time of the treatment period. ORR will be given as proportion together with its 95% confidence intervals (CI). PFS and OS will follow standard definitions and will be estimated using the Kaplan-Meier method. Median PFS and OS will be given together with their 95% CI.

Quality of Life (QoL) will be assessed using the validated EORTC QLQ-C30 and EORTC QLQ-BR23 questionnaires [47, 48]. QoL scales will be derived from single item answers and summarized using appropriate descriptive statistics.

Efficacy will be analysed on the basis of intention to treat (ITT) and thus on all patients enrolled in the study. In parallel, a modified ITT approach will be used in which all patients who received at least one dose of study drugs and who were clinically evaluable [with or without a CT-scan]) will be included. In a separate analysis the per-protocol populations will be analysed which are defined as all patients who received at least one dose of study treatment without major protocol deviations. Major protocol deviations will be determined and documented prior to database lock. The analysis of the modified ITT population will be considered as the primary analysis.

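### The stage 1 look counts 22 treated patients, but the 41 are evaluable patients and only the total is inflated for drop-out; if the planned 10% loss falls after dosing, power is about 77–78%, not 80%

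*Protocol article*

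**What the plan says.** All places are in the Protocol article.

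- **Determination of sample size**, hypotheses: "null hypothesis proportion of 0.2 versus an alternative hypothesis proportion of 0.35 in ORR". The planned type I error is 0.1 and the planned power 80%, which leads to the sample size of 41.
- **Determination of sample size**, first look: "In the first stage, 22 patients will be accrued and treated". The futility rule follows: "The study will be stopped if there are fewer than five patients with either CR or PR".
- **Determination of sample size**, second stage: 19 further patients, again counted as enrolled and treated, bring the total to 41. Success is "12 or more responses out of 41".
- **Determination of sample size**, last paragraph: "Assuming a 10% drop-out rate, 46 patients have to be enrolled for phase 2".
- **Study design** (text after Table 1): "A total of 41 evaluable patients will be included". The Abstract also calls the 41 evaluable.
- **Efficacy analysis**: the modified ITT set takes patients with at least one dose who were clinically evaluable, with or without a CT scan. "The analysis of the modified ITT population will be considered as the primary analysis".

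**The concern.** One go/no-go test is described in three counting units: treated patients (the two-stage rule), evaluable patients (Study design, Abstract and, in effect, the primary analysis set) and enrolled patients (the drop-out allowance). The definition of the modified ITT set makes treated and evaluable different things, because it requires a dose and, separately, clinical evaluability.

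The drop-out allowance protects the final 41 but not the first 22. A patient among the 22 who was dosed but is not evaluable cannot supply a response, while the requirement of 5 responses stays fixed. The first look is then stricter than designed. What is at stake is stopping an active regimen at the interim more often than planned, in a design whose power (0.804) has almost no slack above the stated 0.80.

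**Working it through.** **Inputs.** From Determination of sample size: p0 = 0.20, p1 = 0.35, n1 = 22, continue with at least 5 responses, n = 41, success with at least 12 responses, drop-out 10%, 46 enrolled. The timing of drop-out relative to first dose is not given, so it is varied below. Loss rates of 5% and 15% are assumptions added to show the range.

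**Formula.** For m evaluable patients at stage 1 and 41 at the end, the probability of declaring success at response rate p is

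S(m, p) = Σ over x from 5 to m of P[Bin(m, p) = x] · P[Bin(41 − m, p) ≥ 12 − x].

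The probability of stopping early is P[Bin(m, p) ≤ 4].

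**Step 1: the plan's own figures.** With m = 22:

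- alpha = S(22, 0.20) = 0.0959
- power = S(22, 0.35) = 0.8044
- early stop at 35% = P[Bin(22, 0.35) ≤ 4] = 0.0716
- early stop at 20% = P[Bin(22, 0.20) ≤ 4] = 0.543

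The stated design reproduces, and it is the minimax Simon design for these inputs. The enrolment figure also reproduces: 41 / 0.9 = 45.6, rounded up to 46.

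**Step 2: 10% loss after dosing, as a fixed number.** 22 × 0.9 = 19.8, so take m = 20, with 41 evaluable at the end:

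- early stop at 35% = P[Bin(20, 0.35) ≤ 4] = 0.118
- power = S(20, 0.35) = 0.779
- alpha = S(20, 0.20) = 0.089

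**Step 3: loss after dosing, at random.** Let the stage 1 evaluable number M follow Bin(22, 1 − d) and average S(M, p) over it. Early stop at 35% is P[Bin(22, 0.35(1 − d)) ≤ 4].

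| Loss d after dosing | Early stop at 35% | Power | Alpha |
|---|---|---|---|
| 0% (all drop-out before dosing) | 7.2% | 0.804 | 0.096 |
| 5% | 9.8% | 0.790 | 0.092 |
| 10% | 13.0% | 0.769 | 0.087 |
| 15% | 17.1% | 0.741 | 0.082 |

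**Step 4: loss across all 46.** Suppose each of the 46 is lost with probability 10%, the look is taken after 22 treated, and every evaluable patient is counted against 12. A patient then contributes a response with probability 0.9p, so this is the two-stage rule with 22 and 46 patients at rates 0.18 and 0.315. Power is 0.774 and alpha 0.095.

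**Step 5: both looks in the primary population.** To expect 22 evaluable at 10% loss, 22 / 0.9 = 24.4 patients are needed, that is 24 to 25 enrolled. With 22 and then 41 evaluable, Step 1 applies unchanged: alpha 0.096 and power 0.804.

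**The case against.** The strongest reply is that the power loss depends on when patients drop out. The article does not say whether the 10% leave before or after first dose. If all leave before it and every dosed patient is evaluable, 22 treated are 22 evaluable and power is 80.4%. The modified ITT set also keeps patients without a CT scan, so losses among dosed patients may be few. This stands, and it makes the shortfall conditional. It does not settle the matter, because the analysis set still makes evaluability a condition beyond dosing, and the plan reserves five patients for loss without saying they will be undosed.

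A second reply is that the sample size section is consistent when read alone, since it counts treated patients at both stages. That is true. The mismatch appears only when it is read with Study design, the drop-out allowance and Efficacy analysis. Those sections govern the same test, however.

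Third, the effect is small, and a stricter futility look is conservative for type I error. Both parts are correct.

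A reader might also infer that alpha is breached, because 46 enrolled at 90% evaluable gives more than 41 with probability 0.51, and a cut of 12 at 42 to 46 evaluable patients gives alpha of 0.109 to 0.169 (with 22 evaluable at stage 1). The article does not support this. It ties success to 12 responses out of 41 and nowhere says that a larger number would be tested against 12. Even if all evaluable patients were counted, alpha averages 0.095 once loss is modelled throughout (Step 4).

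**Conclusion.** The point holds as a modest, conditional loss of power. The design is right on its own inputs. If 10% of the treated stage 1 patients are not evaluable, and the final test is on 41 evaluable patients, power is 76.9% (random loss) or 77.9% (exactly 20 evaluable) against the stated 80%. The chance of wrongly stopping at a true rate of 35% is 11.8% to 13.0% instead of 7.2%. The range is 79.0% power at 5% loss, 74.1% at 15%, and 80.4% if nobody is lost after dosing.

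These figures assume that non-evaluable patients contribute no response at the interim, that the requirement of 5 is unchanged, and that evaluability is unrelated to response. Type I error is not at issue on the rule as written: with 41 evaluable at the end it is 0.082 to 0.096 over these scenarios.

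**What to change.** In Determination of sample size, state both looks in the primary population. The stage 1 decision is taken on the first 22 modified ITT patients, with at least 5 responses needed to continue. The final decision is taken on the first 41 modified ITT patients, with at least 12 responses needed for success. This restores alpha 0.096 and power 0.804.

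The cost is wording, plus two to three more patients enrolled before the interim (24 to 25 instead of 22). These lie within the planned 46 at the expected loss (46 × 0.9 = 41.4 evaluable). If loss is random at 10%, 46 enrolled gives fewer than 41 evaluable with probability 0.31, so the text should say whether enrolment continues until 41 are reached.

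If the interim is to stay at 22 treated patients, restate the power as about 77% under 10% loss after dosing. A table of success cut-offs by final evaluable number is not a good substitute. Cuts of 12 up to 41 patients, 13 for 42 to 45 and 14 for 46 hold alpha below 0.10, but average power is only about 77% even with 22 evaluable at stage 1.
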